## Abstract

**Background:**

Antibiotics are over-prescribed for lower respiratory tract infections (LRTI) in nursing home residents due to diagnostic uncertainty. Inappropriate antibiotic use is undesirable both on patient level, considering their exposure to side effects and drug interactions, and on societal level, given the development of antibiotic resistance. C-reactive protein (CRP) point-of-care testing (POCT) may be a promising diagnostic tool to reduce antibiotic prescribing for LRTI in nursing homes. The UPCARE study will evaluate whether the use of CRP POCT for suspected LRTI is (cost-) effective in reducing antibiotic prescribing in the nursing home setting.

**Methods/design:**

A cluster randomized controlled trial will be conducted in eleven nursing homes in the Netherlands, with the nursing home as the unit of randomization. Residents with suspected LRTI who reside at a psychogeriatric, somatic, or geriatric rehabilitation ward are eligible for study participation. Nursing homes in the intervention group will provide care as usual with the possibility to use CRP POCT, and the control group will provide care as usual without CRP POCT for residents with (suspected) LRTI. Data will be collected from September 2018 for approximately 1.5 year, using case report forms that are integrated in the electronic patient record system. The primary study outcome is antibiotic prescribing for suspected LRTI at index consultation (yes/no).

**Discussion:**

This is the first randomised trial to evaluate the effect of nursing home access to and training in the use of CRP POCT on antibiotic prescribing for LRTI, yielding high-level evidence and contributing to antibiotic stewardship in the nursing home setting. The relatively broad inclusion criteria and the pragmatic study design add to the applicability and generalizability of the study results.

**Trial registration:**

Netherlands Trial Register, Trial NL5054. Registered 29 August 2018.

## Background

Lower respiratory tract infections (LRTI) such as pneumonia are common in nursing homes (NHs) [1]. In Dutch NHs in 2015, the incidence of suspected pneumonia was approximately 200 cases per 1000 residents, with a typical pattern of seasonal variation (i.e. winter peak, summer trough) [2]. NH residents are at increased risk of respiratory infections due to factors typical for this population, such as frailty and comorbidities. Also, the crowded nature of NH residence and frequent nursing staff-resident contact may facilitate the transmission of pathogens [1, 3–5]. The incidence of nursing home-acquired pneumonia (NHAP) can be up to tenfold of the incidence in elderly living in the community [1, 6–10]. Moreover, the severity and prognosis of NHAP is worse compared to pneumonia among elderly living in the community [11–13]. NH LRTI episodes may range from self-limiting viral infections, to severe NHAP requiring hospitalization or causing rapid death [3, 14–16].

An early diagnosis of NHAP enables prompt and appropriate management, decreases the risk of complications and mortality, and reduces overall health care costs [16–18]. Yet, physicians often find it difficult to estimate the severity and potential outcome of the LRTI episode [19, 20]. Moreover, NH residents often have atypical clinical presentation, multi-morbidity, and a diminished ability to recall or describe symptoms (e.g. due to cognitive impairment). Diagnostic tools are often not available (e.g. chest X-ray) or applicable (e.g. sputum culture) in this setting [3, 5, 17, 21, 22]. Overall, diagnostic uncertainty often results in (empirical) antibiotic prescribing to be ‘better safe than sorry’. This attitude towards antibiotic prescribing may be reinforced by external factors, such as (perceived) expectations of patients or family members towards antibiotic prescribing [23, 24].

Antibiotics are among the most commonly prescribed drugs in NHs, however, many of these prescriptions are inappropriate [25]. Inappropriate, or ‘unjustified’, antibiotic prescribing for LRTI in NH or care homes ranges from 25 to 98%, according to studies from different settings and with different criteria for defining inappropriateness [21, 22, 26–29]. Overprescribing of antibiotics has possible negative consequences for the patient, such as drug interactions and side effects [21, 27]. At a societal level, overprescribing of antibiotics contributes to the development of antibiotic resistance, which decreases treatment possibilities for future LRTI [5].

C-reactive protein (CRP) point-of-care testing (POCT) is a promising tool to decrease the diagnostic uncertainty regarding suspected LRTI in the NH setting, and therefore decrease inappropriate antibiotic prescribing. CRP is a dynamic biomarker of the presence and severity of inflammation. CRP increases within four to 6 hours after the onset of an inflammatory reaction as well as rapidly decreases after its resolution (4 to 7 hours half-time, and 19 hours half-life) [30–32]. CRP POCT alongside the clinical signs and symptoms may provide the physician with valuable information for the treatment decision [33]. Studies in the general practice population showed CRP to be the strongest predictor of pneumonia, and that the reliability of the diagnosis improves when CRP is added to the evaluation of clinical signs and symptoms [19, 34]. The introduction of CRP POCT in general practice has resulted in a significant and cost-effective reduction in antibiotic prescribing for LRTI in adults as well as in adults with underlying COPD, without negative consequences for clinical recovery [14, 35–37].

At present, CRP POCT is widely used in general practice in several countries, including the Netherlands. In the NH setting, however, (cost-) effectiveness of CRP POCT on antibiotic prescribing for LRTI has not yet been investigated. Consequently, CRP POCT is not commonly used in this setting. However, CRP-values may also have value in this setting. For instance, there is evidence that the CRP-level at index consultation predicts severity and outcome of pneumonia in the elderly population [38, 39].

This study protocol paper describes the design of a cluster Randomized Controlled Trial (RCT) that investigates whether the use of CRP POCT results in a safe reduction in antibiotic prescribing for NH residents with suspected LRTI. Other questions we aim to address are the extent to which CRP POCT values correlate with A) signs and symptoms in NH patients with suspected LRTI, and B) antibiotic treatment. Also, we will evaluate the cost-effectiveness and cost-benefit of the use of CRP POCT in the NH setting.

## Methods/design

### Study design and population

The UPCARE study design is a cluster RCT, with randomization at NH organization level. This randomization level was chosen because of our pragmatic trial design and in order to avoid spill-over effects. Data collection starts September 2018 and will, based on calculations of expected inclusion rate, last approximately 1.5 year. Eleven NH organizations across the Netherlands will participate in the study. A simple randomization procedure using Microsoft Office Excel 2016 software will be performed by the research team to allocate participating organizations to either the control or intervention group (1:1).

Dutch NHs typically have three types of specialized wards: somatic wards that accommodate physically disabled residents, psychogeriatric wards that accommodate residents with dementia, and geriatric rehabilitation wards. NH admission to one of these wards and the required level of care is determined by a standardized assessment performed by a government agency (“Centrum Indicatiestelling Zorg” (CIZ)). Unique to Dutch NHs is the employment of specialized ‘elderly care physicians’. Other NH prescribers may include physicians with other specializations or general medical training, elderly care physicians in training, and nurse practitioners. Dutch NH medical care typically excludes the use of intravenous drugs, and hospital referrals are limited [40, 41].

The study population comprises NH residents from psychogeriatric, geriatric rehabilitation, or somatic wards, who are newly diagnosed with a ‘suspected LRTI’. Patients are excluded if they receive palliative/terminal care with a restrictive antibiotic policy, if they do not wish to be treated with antibiotics, if they are using antibiotics (currently or in the past week), or if they have an infection other than the suspected LRTI (currently or in the past week).

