### Sample size calculation

Based on previous study data [40], we expect 15% less antibiotic prescriptions in the intervention group compared to the control group (i.e. 80% respectively 95%). In order to detect this difference, with 80% power and at a 5% significance level, 146 cases would be required. If we randomize eleven NH organizations with an average number of 400 residents (cluster size) and with an intracluster correlation coefficient of 0.06, the required number of cases is 671 [42].

The expected incidence rate of suspected LRTI is 3.5 cases per 1.000 resident-care weeks in NHs [2]. Based on previous study data, we expect that at most 10% of cases will not meet inclusion criteria and that 75% of eligible cases provide informed consent for study participation. This means that of all LRTI cases, approximately 70% can be included in the study, which translates into an expected 2.4 suspected LRTI per 1.000 resident-care weeks.

ln order to include 671 cases of LRTI in eleven organizations with an average number of 400 residents the study period totals to 1.5 year, with a small margin for potential suboptimal inclusion.

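### Eleven organisations are allocated by simple randomisation without restriction on size or ward mix, and it is unclear whether even a near-equal split is guaranteed

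*Protocol article*

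**What the plan says.** The Study design and population section makes the organisation the unit of allocation ("The UPCARE study design is a cluster RCT, with randomization at NH organization level") and fixes the number of units ("Eleven NH organizations across the Netherlands will participate in the study"). The method follows: "A simple randomization procedure using Microsoft Office Excel 2016 software will be performed by the research team to allocate participating organizations". The ratio given for the two groups is 1:1. No blocking, stratification, matching, minimisation or other constraint is named. The same section describes three ward types with different residents: psychogeriatric, somatic and geriatric rehabilitation.

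The Sample size calculation section gives organisation size only as an average: "If we randomize eleven NH organizations with an average number of 400 residents (cluster size"). It uses an intracluster correlation of 0.06 and arrives at 671 cases. The Data analysis section names no baseline covariate for the primary three-level logistic model. Correction for baseline characteristics is mentioned only for the cost-effectiveness regressions.

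**The concern.** In ordinary usage, simple randomisation means unrestricted, independent draws. With hundreds of units that is harmless. With eleven it can produce a clearly uneven split, and it gives no control over which organisations fall together. A few large organisations, or those with many psychogeriatric beds, could land in one arm.

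Two things are at stake. The first is power, if few organisations receive the intervention. The second is how the result reads: with eleven clusters, a visible difference between arms in size or ward mix is hard to set aside, and the analysis has few between-cluster degrees of freedom for adjustment. Because all eleven organisations are known before allocation, a restricted draw is feasible.

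**Working it through.** **Inputs from the protocol article.** 11 organisations; expected prescribing 80% (intervention) and 95% (control); 80% power; 5% significance (taken as two-sided); ICC 0.06; 146 cases before and 671 after allowing for clustering.

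**Reproducing the plan's figures.** Two proportions, unpooled variance:

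(1.960 + 0.842)² × (0.95×0.05 + 0.80×0.20) / 0.15² = 72.4 per arm, so 73 × 2 = 146.

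Cases per organisation: 671/11 = 61. Design effect: 1 + (61 − 1) × 0.06 = 4.6. Then 146 × 4.6 = 671.6. Both figures reproduce, so the sample size arithmetic is not at fault here.

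**Split probabilities under independent draws (p = 0.5).**

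- 5/6 either way: 2 × C(11,5)/2¹¹ = 2 × 462/2048 = 45.1%, so missed with probability 54.9%.
- 4/7 either way: 2 × 330/2048 = 32.2%.
- 3/8 or worse, either way: 2 × (1 + 11 + 55 + 165)/2048 = 22.7%.
- Four or fewer intervention organisations: (1 + 11 + 55 + 165 + 330)/2048 = 562/2048 = 27.4%.
- Three or fewer intervention organisations: 232/2048 = 11.3%.

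**Power by split.** For *a* intervention and *b* control organisations of 61 cases each:

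SE = √[0.80×0.20 / (61a/4.6) + 0.95×0.05 / (61b/4.6)].

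Power is taken from the noncentral t with 11 − 2 = 9 degrees of freedom and noncentrality 0.15/SE, and from the normal approximation for comparison. Example, 4/7: SE = √(0.16/53.04 + 0.0475/92.83) = 0.0594, and 0.15/0.0594 = 2.53.

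| Intervention/control | Probability | Power, t(9) | Power, normal |
|---|---|---|---|
| 2/9 | 2.7% | 38.7% | 46.4% |
| 3/8 | 8.1% | 51.7% | 61.2% |
| 4/7 | 16.1% | 61.5% | 71.4% |
| 5/6 | 22.6% | 68.3% | 78.1% |
| 6/5 | 22.6% | 72.5% | 81.9% |
| 7/4 | 16.1% | 74.2% | 83.4% |
| 8/3 | 8.1% | 72.9% | 82.3% |
| 9/2 | 2.7% | 66.6% | 76.4% |

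The loss runs mainly one way because the variance is larger in the arm expected at 80% (0.16 against 0.0475), so extra intervention organisations help.

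**Average over all splits** (0/11 and 11/0 counted as zero power):

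- t(9): 66.9%, against (68.3 + 72.5)/2 = 70.4% with the split forced. Loss 3.5 points.
- Normal: 76.3%, against 80.0%. Loss 3.7 points.

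**Balance in size.** The article gives no spread of organisation size. Assuming gamma-distributed sizes with a coefficient of variation of 0.3 to 0.7, simulation puts the chance that one arm holds at least 60% of residents at 53–60% under independent draws and 11–39% with the split forced to 6/5. Forcing the split therefore helps but does not settle balance on size.

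**The case against.** The strongest reply is that the article does not define the Excel step. A list of eleven put in random order and cut at six and five fits the words, including the stated 1:1 ratio, as well as eleven coin tosses do. On that reading the uneven-split probabilities and powers fall away. This stands, and so the split figures hold only conditionally. An exact 1:1 split of eleven is impossible under any method and is no error. Nor is the use of Excel.

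A reader might infer that any uneven split lowers power. The document's own rates do not support that: 7/4 does slightly better than 6/5, and 8/3 matches it. Nor should the gap between the t(9) figures and the planned 80% be blamed on allocation. At 5/6 the change from normal to t(9) alone takes power from 78.1% to 68.3%, which is a separate matter.

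A reader might also infer that simple randomisation biases the primary comparison. It does not: chance imbalance adds variance, not bias in expectation, and between-organisation variation is already represented by the ICC of 0.06. The article reports no individual sizes, ward mixes or prior prescribing, so no actual imbalance can be shown.

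Finally, covariates may be specified in an analysis plan that is not shown. Their absence here is not itself a fault. But an analysis plan cannot change the allocation method, which the article states.

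**Conclusion.** The point holds as a worthwhile design improvement, not as an invalidity. On either reading of the allocation sentence, nothing balances organisation size or ward mix across eleven clusters. On the independent-draw reading there is also a 27% chance of four or fewer intervention organisations, with power of 62% at 4/7 and 52% at 3/8 against 68–73% at a near-equal split. The average cost is modest, about 3.5 points, and splits of 7/4 or 8/3 favouring the intervention cost nothing.

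The power figures assume 61 cases in every organisation, the plan's rates and ICC, a two-sided 5% test and 9 degrees of freedom. The size-imbalance range rests on an assumed spread of organisation sizes.

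**What to change.** State that the split is forced to 5/6 or 6/5. List the 2 × 462 = 924 such allocations, keep those balanced on number of residents and ward mix (and prior-year antibiotic prescribing if it can be obtained), and draw one at random with a recorded seed. Include the constraint variables in the primary model.

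Data collection was to start in September 2018, so the draw may already have been made. In that case report how it was done and the resulting split, and prespecify adjustment of the primary model for ward type at patient level and for organisation size.

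The cost is a few hours of programming, the organisation-level data, and one between-cluster degree of freedom for each organisation-level covariate: size alone takes 9 to 8. The list of such covariates should therefore stay short.

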### Sample size calculation

Based on previous study data [40], we expect 15% less antibiotic prescriptions in the intervention group compared to the control group (i.e. 80% respectively 95%). In order to detect this difference, with 80% power and at a 5% significance level, 146 cases would be required. If we randomize eleven NH organizations with an average number of 400 residents (cluster size) and with an intracluster correlation coefficient of 0.06, the required number of cases is 671 [42].

The expected incidence rate of suspected LRTI is 3.5 cases per 1.000 resident-care weeks in NHs [2]. Based on previous study data, we expect that at most 10% of cases will not meet inclusion criteria and that 75% of eligible cases provide informed consent for study participation. This means that of all LRTI cases, approximately 70% can be included in the study, which translates into an expected 2.4 suspected LRTI per 1.000 resident-care weeks.

ln order to include 671 cases of LRTI in eleven organizations with an average number of 400 residents the study period totals to 1.5 year, with a small margin for potential suboptimal inclusion.

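### The sample size of 671 rests on about 61 cases per organisation, not on the 400 residents labelled as cluster size, and the 80% power makes no allowance for few or unequal clusters

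*Protocol article*

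**What the plan says.** The protocol article (Sample size calculation) expects antibiotic prescribing of 95% in control and 80% in intervention organisations. It first gives the size without clustering: "with 80% power and at a 5% significance level, 146 cases would be required". It then adjusts for "eleven NH organizations with an average number of 400 residents (cluster size) and with an intracluster correlation coefficient of 0.06" and concludes that "the required number of cases is 671".

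The same section uses the 400 residents a second time, with an expected 2.4 included cases per 1,000 resident-weeks, to derive the study duration: "the study period totals to 1.5 year, with a small margin for potential suboptimal inclusion".

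Under Study design and population, the unit of randomisation is the organisation: "The UPCARE study design is a cluster RCT, with randomization at NH organization level". Allocation is simple and 1:1. Under Data analysis, the primary model is a three-level logistic regression, reducible to two levels, estimated by second-order penalised quasi-likelihood (PQL). The article gives no number of cases per organisation, no spread of organisation sizes and no reference distribution for the test.

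**The concern.** The design effect needs the number of analysed cases per cluster. The 400 residents are the population in which cases arise, yet the text attaches the term cluster size to them in the same sentence as the ICC. A reader who follows the text gets a requirement more than five times the stated one and cannot tell which figure is meant.

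The second matter is the power itself. The treatment contrast is between eleven randomised organisations, so it has about 11 - 2 = 9 degrees of freedom. A calculation with normal critical values and equal clusters allows neither for that nor for organisations of different size. If 80% is too favourable, a non-significant result could be read as stronger evidence against a 15-point reduction than it is. The planned recruitment margin would offer little protection, because extra cases within the same eleven organisations reduce the variance only slightly.

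**Working it through.** **Inputs.** From the protocol article: 95% and 80%; two groups; 5% significance (two-sided reproduces the figure); 80% power; 11 organisations; ICC 0.06; 400 residents per organisation; 2.4 cases per 1,000 resident-weeks; 1.5 years. Assumed, because no figure is given: coefficient of variation (CV) of cases per organisation between 0 and 0.6.

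**1. The unadjusted size.** With unpooled variance, n per arm = (0.95 x 0.05 + 0.80 x 0.20) x (1.960 + 0.842)^2 / 0.15^2 = 72.4, so 73 per arm and 146 in total. This reproduces.

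**2. The clustered size.** N = 146 x [1 + (m - 1) x 0.06].
- m = 671/11 = 61: design effect 1 + 60 x 0.06 = 4.6; N = 671.6. This reproduces. The version for a fixed number of clusters, 146 x 0.94 / (1 - 146 x 0.06/11), gives 674.
- m = 400: design effect 1 + 399 x 0.06 = 24.94; N = 3,641. This does not reproduce.

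**3. Power at 671, equal clusters.** With 335.5 cases per arm, SE = sqrt(4.6 x 0.2075 / 335.5) = 0.0533 and 0.15/SE = 2.81.
- Normal reference: 80.3%, the stated power.
- Noncentral t with 9 degrees of freedom (critical value 2.262): 70.7%.
- Eleven cannot be halved. With five control and six intervention organisations the 9-df figure is 72.5%; with six control and five intervention it is 68.3%.

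**4. Unequal sizes, 9 degrees of freedom.** The conservative design effect is 1 + [(1 + CV^2) x 61 - 1] x 0.06. The efficient-weighting version divides 4.6 by 1 - CV^2 x a(1 - a), where a = 61/(61 + 0.94/0.06) = 0.796.

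| Assumed CV | Conservative: design effect, power | Efficient weighting: design effect, power |
|---|---|---|
| 0 | 4.60, 71% | 4.60, 71% |
| 0.4 | 5.19, 66% | 4.72, 70% |
| 0.6 | 5.92, 60% | 4.89, 68% |

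**5. Detectable difference at 80% power, 9 df.** Holding control at 95% and using the conservative design effect: about 17 points with equal sizes, 19 at CV 0.4 and 20 at CV 0.6.

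**6. The recruitment margin.** 11 x 400 = 4,400 residents; 4,400 x 2.4/1,000 = 10.56 cases a week. So 671 cases take about 64 weeks, and 78 weeks yield about 824. At 824 equal-cluster cases the 9-df power is 72.3%. With unlimited cases the SE tends to sqrt(0.06 x 0.2075/5.5) = 0.0476, and power to about 80.1%.

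**7. Sensitivity.** With 9 df and equal sizes, 671 cases give 83% at ICC 0.04 and 61% at ICC 0.08. A simulation of a logistic model fitted by second-order PQL and tested on 9 df (five control and six intervention organisations) gave 81% with equal sizes and 77% at CV 0.5. A cluster-level t-test in the same setting gave 73% and 71%. These simulations were not rerun for this check, and the scale on which the ICC was imposed is not recorded, so they are indicative only.

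**The case against.** The strongest reply is that the planners did the right sum. The figure 671 is 11 x 61, it reproduces from the stated ICC, and 400 is used correctly as the resident pool for accrual. On this view the fault is one parenthesis. That stands: a reader might infer that 671 is an arithmetic error or that the trial needs 3,641 cases, and the document supports neither. Nor does the calculation ignore the eleven organisations, since 61 cases each comes from dividing by eleven. What it leaves out is narrower: the few degrees of freedom and any variation in size.

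The second reply is that the planned analysis is a multilevel logistic model, not a test of a risk difference. The 9-df reference is added here; the article states none, and such detail may sit in a document not shown. The simulation of a logistic PQL model gives about 77-81%, close to the stated power. This also stands in part. It means the size of the shortfall is not settled, and that 71% should not be quoted as the trial's true power. It does not rescue the statement as written, because the published 80% comes from the normal, equal-size formula, and that same formula gives about 71% once the degrees of freedom are counted.

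Third, no CV is given. The word average suggests that sizes differ but does not say by how much, so the loss from unequal sizes is a range under an assumption. With efficient weighting, which is nearer to what a mixed model does, it is only 1 to 3 points below 71%. The ICC matters at least as much. Finally, the method cited for the calculation could not be consulted.

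**Conclusion.** The point holds in two parts of different firmness.

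The mislabelled input is certain and does not depend on method: 671 cannot be obtained from a cluster size of 400, and it is obtained from 61 cases per organisation.

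The power statement is optimistic on its own formula: 80.3% with normal critical values, about 71% with 9 degrees of freedom and equal sizes, and about 60-70% if the CV lies between 0.4 and 0.6, depending on weighting. These figures assume a common ICC of 0.06 and a comparison on the risk-difference scale. A reader might conclude that the trial is shown to be badly underpowered. The documents do not support that: the logistic simulation lies at 77-81%, and a lower ICC of 0.04 would give 83% even with 9 degrees of freedom. What can be said is that 80% is the favourable end of a plausible range, and that on this formula recruiting beyond 671 within the same eleven organisations changes little (72% at 824).

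**What to change.** In the sample size section:

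- Give the cluster size as 61 analysed cases per organisation (671/11), with design effect 4.6. Keep the 400 residents per organisation only as the pool used for accrual.
- Restate power with 9 degrees of freedom and the actual spread of organisation sizes, preferably by simulating the planned multilevel logistic model with the scale of the ICC stated. Alternatively, state the difference detectable with 80% power; on the formula this is about 17 points with equal sizes, 19 at CV 0.4 and 20 at CV 0.6.
- Show the result for a small range of ICC values.
- Say that the recruitment margin guards against slow inclusion and adds little power beyond 671 cases.

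The cost is wording and one short simulation. No patients, organisations or procedures change. The downside is that the stated power becomes less favourable.
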